#### Functional tests

The Biomec 400 v1.1™ force plate (EMG System do Brasil (EMG System do Brasil Ltda® - http://www.emgsystem.com.br - [name]. [name]) will be used for the stabilometric analysis. This system quantifies the distribution of vertical ground reaction force in a static or dynamic position with a sampling frequency of 40 Hz using four sensors (two anterior and two posterior) capable of supporting 150 Kg. Each sensor stores analog data, which are amplified, converted into digital data, recorded, and interpreted using the Biomec 400™ software program (EMG System do Brasil (EMG System do Brasil Ltda® - http://www.emgsystem.com.br - [name]. [name]). The distribution of force on the four points and changes in body sway in the anteroposterior (y axis) and mediolateral (x axis) directions will be evaluated using mean displacement and area. The force plate will be placed on a flat surface, which will be verified by levels attached to the extremities of the plate. The participants will be positioned as follows: in quiet, standing, barefoot, feet abducted at 30° and separated by 3 cm, arms alongside the body, and gaze fixed on a round target (5 cm in diameter) at the height of the glabellum positioned on a pedestal 1.5 meters from the participant. Two stabilometric readings will be performed under two different conditions (eyes open and eyes closed). Each reading will last 30 seconds, with a one-minute interval between readings.

A portable dynamometer (Lafayette manual muscle system, model 01163, Lafayette Instrument Company, Lafayette, Indiana, United States) will be used. This device has been broadly employed in clinical practice and scientific procedures due to its good inter-examiner and intra-examiner reliability in comparison to other evaluation measures considered the gold standard for this type of evaluation [18,19]. Four five-second readings will be taken of maximum voluntary isometric contraction (MVIC) with a 30-second rest period between contractions. The participant’s hands will be crossed over the chest. Readings will be made of the quadriceps and gluteus medius, bilaterally. The first MVIC will be to familiarize the participant with the task. If a participant is unable to performed three contractions with less than 10% variability, a new set of readings will be performed. Strong, constant, verbal stimuli will be given throughout the test. The order of the MVIC readings will be randomized to avoid bias. The procedure for the gluteus medius readings will be: Participant lying on one side with the limb to be tested on top in neutral position, maintained using pillows placed between the legs. An adjustable non-elastic strap will be placed over the iliac crest and attached around the cot to stabilize the pelvis. The dynamometer will be positioned over the lateral femoral condyle under a non-elastic strap attached around the distal thigh and cot. MVIC will be solicited in the form of hip abduction [20]. The procedure for the quadriceps readings will be: Participant in the sitting position, hip flexed at 90° and knee flexed at 60°. The dynamometer will be positioned at the level of the malleoli in the anterior region under a non-elastic strap attached around the distal tibia and cot. MVIC will be solicited in the form of knee extension [21]. Strength data, measured in kilograms (Kg), will be normalized by body weight (Kg) using the following formula: Kg (muscle strength)/Kg (body mass) × 100 [18,22]. The mean of three normalized readings will be considered for the analysis.

A digital algometer (Instrutherm™, model DD-200 (Instrutherm instrumentos de medição Ltda, São Paulo, Brazil) will be used to determine the pressure pain threshold. The participant will be positioned lying on one side on the cot and eight points will be marked on the knee(s): Point 1 - 2 cm below the medial edge of the patella; Point 2 - 2 cm below the lateral edge of the patella; Point 3 - 3 cm to the side of the midpoint of the lateral border of the patella; Point 4 - 2 cm above the lateral edge of the patella; Point 5 - 2 cm above the highest point of the upper edge of the patella; Point 6 - 2 cm above the medial edge of the patella; Point 7 - 3 cm to the side of the midpoint of the medial edge of the patella; and Point 8 - center of the patella [23]. A previously trained examiner will position the algometer perpendicular to each point and apply gradual pressure at a constant rate of approximately 0.5 kg/cm^2^/s. The points will receive pressure until the participant reports feeling pain and the value in kg/cm^2^ registered on the readout of the equipment will be recorded. The pressure pain threshold will be measured three times on each of the eight points, with the mean value of each point considered for the analysis.

A fleximeter (pendular goniometer; Sanny™(American Medical do Brasil Ltda, São Bernardo do Campo, Brazil) will be used for the evaluation of knee flexion. The participant will be placed in the prone position with the ankles off of the end of the cot. The fleximeter will be positioned on the lateral face of the ankle with the display turned toward the researcher. The researcher will stabilize the pelvis so that it does not move. For the evaluation of extension, the movement will begin with maximum knee flexion. The evaluation will be performed on both lower limbs. Two repetitions of each movement will be performed and the mean will be used for analysis [24].

The Timed up-and-go test (TUGT) is used to evaluate functional mobility by the time required for the participant to stand up from a chair, walk three meters, turn around, walk back to the chair, and sit down again. A chronometer (OREGON™ (Oregon Scientific Brasil LTDA – http://www.oregonscientific.com.br - [name]. [contact]) will be started after the verbal command ‘go’ and stopped when the participant has returned to the initial sitting position. The test will be performed twice. The first trial will be to familiarize the participant with the procedure and the time required to complete the second trial will be recorded. An armless chair with an adjustable height will be used to adjust the position of the knees of each individual at 90° flexion [25]. The following reference values will be considered: 10 seconds for healthy, independent adults with no risk of falls; 11 to 20 seconds for elderly individuals with disability or frailty; and more than 20 seconds indicates important mobility deficit and a risk of falls [26].

The Functional reach test (FRT) defines the maximum forward functional reach beyond one’s arm length while maintaining a fixed-foot base. A reach of less than 15 cm indicates frailty and an eminent risk of falls [27]. A metric tape will be attached to the wall parallel to the floor at the height of the acromion of each individual. The participant will be barefoot with feet parallel to the wall and near the beginning of the metric tape with the wrists in neutral position, elbows extended, and shoulder flexed at 90°. The individual will be instructed to lean the body forward without touching the tape. The movement of the wrist over the tape will be read. Three readings will be made, with the mean value used in the analysis.

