### Inclusion criteria

The inclusion criteria are as follows: diagnosis of OA of the knee (bilateral) confirmed by the participant’s physician according to criteria of the American College of Rheumatology; Grades 2 to 4 on the Kellgren-Lawrence OA scale (0 = absence of OA, 1 = doubtful, 2 = minimal, 3 = moderate, and 4 = severe); aged between 40 and 80 years; either gender; and knee pain and functional disability for at least three months, as confirmed by the medical history of each patient. The participants will be allowed to use medications prescribed by their doctor. The use of analgesics or anti-inflammatory drugs will be monitored throughout the study. The name, dosage, and frequency of the medications will be recorded and presented in a table.

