#### Data analysis

The sample size was calculated using the MVIC of the muscles as the outcome and an 80% power to detect a 20% improvement, with a 5% level of significance. Based on the study by Alfredo *et al.*[28], a minimum of 17 patients were determined for each group.

Primary (MVIC of the muscles (dynamometer) and stabilometry) and secondary (pain (digital algometer), range of motion (fleximeter), and quality of life (WHOQOL-BREF and WOMAC ) outcomes will be assessed.

Descriptive statistics will be used, and data will be summarized using mean, standard deviations, and percentiles. Normality of data distribution will be tested using the Kolmogorov-Smirnov test. Normal variables and comparison among three groups of the study will be assessed at baseline and at eight weeks follow-up using Analysis of Variance. Post-hoc tests will consist of the Turkey test for parametric variables, and the Dunn’s test for non-parametric variables, and the Dunn’s test for non-parametric variables. Data processing will be performed using the SPSS™ version 13.0 (Chicago, Illinois, United States) and the level of significance will be set to 5%.

The Cohen's d method will be used to determine the effect size. The interpretation of the values will be based on the classification established by Cohen: less than 0.2 (small effect); around 0.5 (moderate effect), up from 0.8 (large effect) [29].

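### Muscle strength and range of motion are defined per limb in patients with two affected knees, and the plan does not say how two limbs become one value per patient; pooling them would inflate the type I error

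*Protocol article*

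**What the plan says.** The inclusion criteria of the protocol article require "diagnosis of OA of the knee (bilateral) confirmed by the" participant's physician, so each participant contributes two diseased knees. Allocation to the three groups is by participant (Overview of research design).

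Under Functional tests, three outcomes are taken at limb level:

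- **MVIC (primary).** "Readings will be made of the quadriceps and gluteus medius, bilaterally". Four contractions are recorded and the first is for familiarization. Then: "The mean of three normalized readings will be considered for the analysis".
- **Range of motion (secondary).** "The evaluation will be performed on both lower limbs", and "Two repetitions of each movement will be performed and the mean will be used for analysis".
- **Pressure pain threshold (secondary).** Eight points are marked and each is read three times, "with the mean value of each point considered for the analysis". The wording leaves open whether one knee or both are marked.

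The Data analysis section plans a "comparison among three groups of the study will be assessed at baseline and at eight weeks follow-up using Analysis of Variance", with Tukey or Dunn post-hoc tests at a 5% level. It sizes the trial on MVIC at a minimum of 17 patients per group. It names no participant term, no limb term, and no step from two limbs to one value per patient.

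**The concern.** One-way ANOVA, Tukey's test and Dunn's test all assume that the observations within a group are independent. Two limbs of one person are not: they share body size, age, fitness, medication, pain behaviour, the exercise programme and the allocation. If each limb is a record, the analysis appears to have 34 observations per arm when only 17 people were randomised, and the standard error of a group mean is too small.

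The other way to use the per-limb values as they stand is to test right and left separately. That respects independence within each test, but it turns MVIC into four primary comparisons (two muscles by two limbs), and no rule says which one counts. Tukey's procedure protects across pairs of groups, not across limbs or muscles.

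With 51 participants, the choice between these routes could decide whether the outcome on which the trial was sized is called significant. Left open, it can be made after the data have been seen.

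**Working it through.** **Inputs from the protocol article.** 3 groups; 17 patients per group; 2 limbs per patient, hence 17 × 2 = 34 limbs per group and 3 × 34 = 102 in all; 5% significance level.

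**Assumptions.** Two-sided testing, as sidedness is not stated. A between-limb correlation ρ, not given in the document, is shown over 0.3 to 0.9.

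**Step 1. The plan's own figure.** The article gives 80% power, a 20% improvement and 17 per group, but no standard deviation, so 17 can be neither confirmed nor refuted. For a two-group comparison of means it corresponds to a standardised difference of √(2/17) × (1.960 + 0.842) = 0.96. That is a standard deviation of 0.20/0.96 ≈ 21% of the mean if the 20% is relative to the mean. The calculation counts patients.

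**Step 2. How many values per person the text yields.** Three retained readings on each of two limbs make six readings per muscle. A mean of three is therefore a within-limb mean. Two repetitions on each of two limbs make four per movement, so a mean of two is again within a limb. Read literally, each person has two values per muscle and per movement.

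**Step 3. Both limbs entered as independent records.** The true variance of a group mean is σ²(1 + ρ)/34, whereas the ANOVA uses about σ²/34. The effective number of observations is 34/(1 + ρ). The two-group type I error is approximately 2 × [1 − Φ(1.96/√(1 + ρ))]. For ρ = 0.5 this is 2 × [1 − Φ(1.60)] = 0.110. The three-arm F-test error was simulated with no true effect (50,000 trials per ρ).

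| ρ (assumed) | 1 + ρ | Effective n per arm | Two-group type I error | Three-arm F-test type I error |
|---|---|---|---|---|
| 0.3 | 1.3 | 26.2 | 0.086 | 0.099 |
| 0.5 | 1.5 | 22.7 | 0.110 | 0.137 |
| 0.7 | 1.7 | 20.0 | 0.133 | 0.176 |
| 0.8 | 1.8 | 18.9 | 0.144 | 0.196 |
| 0.9 | 1.9 | 17.9 | 0.155 | 0.217 |

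A separate simulation of 40,000 replicates agrees: 0.140, 0.178 and 0.211 for the F test, and 0.112, 0.138 and 0.156 for the two-group t test, at ρ = 0.5, 0.7 and 0.9.

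**Step 4. Right and left tested separately.** Each F test holds 5%. The simulated chance that at least one of the two is significant for a given muscle falls from 0.096 at ρ = 0.3 to 0.071 at ρ = 0.9.

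**Step 5. One value per participant.** With the mean of the two limbs, or a single limb, the simulated F-test error stays at 0.049–0.052 over the same range of ρ.

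**The case against.** The strongest reply is that the article never says limbs enter as separate records. A reader might infer from the per-limb definitions that pooling is planned and that the error rate will therefore be inflated. The text does not support that. The only unit the Data analysis section names is the patient, which fits one value per patient. The sentences on averaging say how repeated readings are reduced; they do not forbid a later step that averages the limbs or selects an index limb, and either would keep the ANOVA valid. Such a rule may also sit in an analysis plan that is not shown, and an article need not repeat it.

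Most of this stands. The inflation is conditional on pooling, the limb correlation is assumed, and separate right and left tests raise a question of multiplicity, not of independence. The scope is limited too: stabilometry (the other primary outcome), TUGT, FRT and the questionnaires are whole-person measures, and for algometry it is not explicit that both knees are tested.

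What does not fall away is that the article itself specifies the value to be analysed for a primary outcome and stops at the limb. This is a definition given incompletely, not a topic left untouched. Averaging the limbs would mean six readings where three are specified, and no index limb is named. An analyst has to add a step to reach a valid analysis; one who follows the text literally has two values per person.

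**Conclusion.** The point holds in conditional form. For MVIC and range of motion, and for pain threshold if both knees are tested, the analysed value is defined per limb while randomisation and sample size are per patient, and nothing connects the two. If limbs are pooled in the named ANOVA, the three-arm type I error is about 10–22% instead of 5%. If right and left are tested separately, the chance of at least one false positive is about 7–10% per muscle. Both ranges assume a limb correlation of 0.3–0.9, 17 patients per group with both limbs measured, and normally distributed values. It cannot be concluded that the trial's error rate is inflated, only that the plan as written does not exclude it for one of its two primary outcomes.

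**What to change.** In the Data analysis section, state that each participant contributes one value per outcome: the mean of right and left limbs for each muscle, each movement and the pain threshold. Compare these means between groups at eight weeks, adjusted for the same mean at baseline. Averaging the limbs is what restores the 5% level; the baseline adjustment is an added gain in precision and is not needed for this point. If limb-level data are preferred, use a mixed model with a random participant effect, so that the group comparison is judged against variation between participants. State also whether algometry covers both knees.

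The cost is a sentence or two, with no new data or visits. The drawback is that separate left and right claims are given up.

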Low-level laser therapy (LLLT) has properties that exert a positive influence on the proliferation of fibroblasts, collagen synthesis, and bone regeneration. LLLT also has an analgesic effect mediated by hormonal and opioid mechanisms and has therefore recently become an important tool in the treatment of OA, offering pain relief and improved knee function [9,10]. The use of phototherapy in the form of LLLT and light-emitting diode therapy, both of which operate in the red and infrared spectra, has proven effective in delaying the development of fatigue and improving muscle performance [11]. It would therefore seem advantageous to combine these two forms of phototherapy in a single device. However, clinical trials are needed to test the effects on deeper structures, such as joints, using comparable protocols and outcome measures. Due to its physiological effects, phototherapy may promote increased positive effects of preexisting treatments and may slow the degeneration process and its repercussions, such as contractures and joint deformity, which can lead to postural imbalance and the loss of muscle strength in the lower limbs, resulting in recurrent falls.

The aim of the proposed study is to analyze the effect of the incorporation of phototherapy into a therapeutic exercise program for OA of the knee. The hypothesis is that patients with OA of the knee who are treated with phototherapy combined with a therapeutic exercise program will experience a greater reduction in pain as well as improved knee range of motion, static balance, functional capacity, muscle strength, and quality of life in comparison with those treated with exercise alone.

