### Procedures

#### Questionnaires and scales

The following questionnaires and scales will be administered before and after the treatment protocols: Lower Extremity Functional Scale: Scale consisting of 20 items developed to evaluate musculoskeletal dysfunction in the lower limbs [12]. The scores for each item are 0 (extreme difficulty or unable to perform the activity), 1 (quite a bit of difficulty), 2 (moderate difficulty), 3 (a little bit of difficulty), and 4 (no difficulty). The maximum score is 80 points [13]. Numeric pain rating scale: A simple, easily administered scale made up of a set of numbers ranging from 0 (absence of pain) to 10 (worse pain imaginable) [14]. The degree of pain in the knee(s) with OA will be measured with the participant at rest, before the use the algometry. Quality of life will be evaluated using the WHOQOL-BREF, which is a short version of the WHOQOL-100 developed by the Quality of Life Group of the World Health Organization. The WHOQOL-BREF is made up of 26 items: two addressing overall health and the others divided among four subscales (physical health, psychological health, social relations, and environment). Each item is scored based on a Likert scale ranging from 1 to 5 points. At the end of the study, the results will be transformed into a linear scale ranging from 0 to 100, with higher scores denoting a better quality of life [15,16]. Besides being administered during the initial and final evaluations, the WHOQOL-BREF will also be administered three and six months after the final evaluation through telephone contact.The WOMAC is a specific index for the evaluation of pain, stiffness, and physical function in individuals with OA of the knee and/or hip. This index offers separate scores for the different subscales and contains 24 items: five on pain (score: 0 to 20); two on stiffness (score: 0 to 8), and 17 on physical functioning (score: 0 to 68) [17]. Higher scores indicate worse pain, stiffness, and functional limitation. All questionnaires and scales will be administered in a private room and the participants will be instructed to fill out all items. If a participant refuses or is incapable of cooperating, the researcher will mark the exam with the letters ‘NR’, denoting ‘not registered’, and will also write down the reason for the refusal or inability to complete the questionnaire. All assessment tools will be administered without time constraints to avoid the occurrence of rushed responses.

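### Pressure pain threshold is carried to the analysis point by point, so the secondary outcome labelled pain becomes eight unadjusted tests per knee; one score per participant should be named

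*Protocol article*

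**What the plan says.** The algometry paragraph under Functional tests sets the sites, "eight points will be marked on the knee(s"), and then the variable: three readings are taken per site, "with the mean value of each point considered for the analysis". Averaging is over the three readings within a point. No mean over the eight points, and no rule for the two knees, is given.

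Inclusion criteria ask for a "diagnosis of OA of the knee (bilateral"), so both knees are affected.

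The Data analysis section lists the secondary outcomes: "secondary (pain (digital algometer), range of motion (fleximeter), and quality of life (WHOQOL-BREF and WOMAC ) outcomes will be assessed". Algometry is the only entry labelled pain. The same section plans analysis of variance across the three groups at a 5% level, with Tukey or Dunn post-hoc tests. It mentions no lead point, no multi-site model and no adjustment across points.

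The Background names pain first among the expected benefits: patients given phototherapy with exercise "will experience a greater reduction in pain".

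**The concern.** Elsewhere in Functional tests, wording of the same kind fixes the analysis variable: the mean of three normalised strength readings, of two range-of-motion repetitions, of three reach readings. Read the same way, the algometry sentence fixes eight variables per knee. Each would have its own three-group test at 5%, and nothing says which of them answers the pain question.

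If any one significant point can be reported as pain relief, the error rate for that statement is well above 5%. Pain is the first benefit in the hypothesis, so readers will look for this result.

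**Working it through.** **Plan's own figure.** The article gives no sample size or error rate for pressure pain threshold, so there is none to reproduce. The 17 per group was derived for muscle strength and is used here only as the group size.

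**Inputs from the article.** Eight points per knee; two knees; three groups; 17 per group (51 in all); 5% per test.

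**Assumptions.** Two-sided tests, normal data, and the same correlation r between every pair of points. The article gives no r, so a range is shown.

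**Step 1: upper bound, independent tests.** Chance of at least one false positive = 1 − 0.95^m.
- m = 8: 1 − 0.95^8 = 0.337
- m = 16: 1 − 0.95^16 = 0.560

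**Step 2: correlated points, no true effect, overall three-group test.** Simulated with 3 × 17 participants; a single score has 5%. Repeat runs differ by about one percentage point.

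| r | at least one of 8 points | at least one of 16 points |
|---|---|---|
| 0.4 | 28% | 44% |
| 0.6 | 23% | 34% |
| 0.8 | 17% | 22% |
| 0.9 | 12% | 15% |

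The 16-point column applies only if each knee is tested separately, and it takes the same r between knees as within a knee.

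**Step 3: the comparison that isolates phototherapy.** For active versus placebo by the Tukey test, one variable has a false-positive chance of about 2%. The chance of at least one such result over eight points is about 12%, 10% and 7% at r = 0.4, 0.6 and 0.8.

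**Step 4: what averaging does to precision.** Variance of the eight-point mean relative to one point = (1 + 7r)/8.
- r = 0.4: 3.8/8 = 0.475
- r = 0.6: 5.2/8 = 0.65
- r = 0.8: 6.6/8 = 0.825
- r = 0.9: 7.3/8 = 0.9125

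**Step 5: power, by illustration.** Take a shift of 0.7 single-point SD at every point and an unadjusted two-sample t-test with 17 per arm. Effect on the mean in SD units = 0.7/√((1 + 7r)/8).

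| r | one pre-chosen point | mean of eight | any of eight, uncorrected |
|---|---|---|---|
| 0.4 | 51% | 82% | 93% |
| 0.6 | 51% | 69% | 86% |
| 0.8 | 51% | 59% | 76% |

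The mean beats a single pre-chosen point. It does not beat the uncorrected any-point rule, which gains its extra power by paying the error rates in steps 2 and 3.

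**Step 6: effect at six of eight points.** The shift of the mean is 0.7 × 6/8 = 0.525. Divided by √0.475, √0.65 and √0.825 this is 0.76, 0.65 and 0.58 SD, giving power of about 58%, 45% and 37%, against 51% for one responding point.

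**The case against.** The strongest reply is that the sentence only explains how repeat readings become one value per point. No sentence plans an analysis of variance at each point, none says that any significant point will count as pain relief, and an analysis plan that is not shown may define a summary. This stands in part: the test count is what follows if the article is applied as written. But the sentence names the value that goes into the analysis, and a summary score would have to depart from it. That is a stated choice to correct, not a detail left for later.

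Four stronger readings are tempting and are not supported.
- *There will be 16 tests.* This needs the knees to be analysed separately, which the article does not say. Eight per knee is what the text supports.
- *The three pairwise comparisons multiply the problem again.* The Tukey test controls the comparisons among groups within one point. What it leaves open is the set of points.
- *A real effect is easier to miss.* Under the uncorrected any-point rule it is easier to find (step 5). Averaging gains power only over a single pre-chosen or corrected point, and only if the effect is fairly uniform.
- *Pain rests on algometry alone.* That is true of the label only. WOMAC, listed under quality of life, has its own pain items, "five on pain (score: 0 to 20"), and a numeric pain rating is collected, though it is not in the outcome list.

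Averaging is also not free. The Phototherapy section treats the medial, lateral and posterior quadrants, whereas points 5 and 8 lie above and at the centre of the patella. An effect at only some points is therefore conceivable, and step 6 shows that the mean can then do worse than one responding point.

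**Conclusion.** The concern holds as a multiplicity point on a secondary outcome. Applied as written, the article gives eight unadjusted tests per knee for the outcome labelled pain. Over r = 0.4 to 0.8, the chance of at least one false-positive overall test falls from about 28% to 17%, and it is still 12% at r = 0.9, against 5% for one score. On the active-versus-placebo comparison the inflation is smaller in absolute terms, about 12% to 7% against about 2%.

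The sizes depend on the assumed equal correlation; the direction does not, since every value tried gave inflation. The sample size and the primary outcomes (muscle strength and stabilometry) are not touched, and another pain score is collected, so the weight is minor to moderate.

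**What to change.** Replace the end of the algometry paragraph with a rule of this kind: the pressure pain threshold score for each participant is the mean of the eight point values, averaged over both knees; only this score is tested between groups; values at single points are reported descriptively. If site patterns are of interest, one mixed model with point and knee as repeated factors, and a single pre-stated group comparison, would also serve.

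The change is one sentence and leaves data collection as it is. It should be made before unblinded results are seen. Its price is that an effect limited to some points is diluted in the score, as step 6 shows, and would be visible only in the descriptive table.
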